##### Dietary energy restriction

3.2.1.3.

Estimated daily energy intake will be measured via a food diary for the 7 days leading into baseline, Week 24 (end of active interventions) and the 18-months follow-up. Participants will choose to complete the food diary either by a paper record or an online food diary equivalent (“Research Food Diary App”, Xyris Software Pty Ltd., Australia) depending on participant preference. Both these methods have been shown to result in similar nutrient intake estimates for participants following a weight loss intervention (27). Participants will be encouraged to complete the food diary in real time to minimize the potential of recall bias if diaries are completed retrospectively. The food diary will be entered into Foodworks 7 (Xyris Software Pty Ltd., Australia) to calculate total daily energy intake. The 24-week and 18-month average daily energy intake will be divided by the baseline average daily energy intake to provide an estimate of the percent change in energy intake achieved at each time-point. See Objective 1.3 in Table 1.

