## Intervention of interest

2.

The full study protocol has been described previously (11). In summary, shift workers will be randomized to one of three dietary interventions including: 20% continuous daily energy restriction (CER), versus 5:2D (day fast twice per week), versus 5:2N (night fast twice per week aligning with a night shift) for 24-weeks with a 12-month follow-up period. In the 5:2 interventions, participants will aim to limit intake for each fasting period to 2,100 kJ/day (females) or 2,500 kJ/day (males), providing a weekly energy restriction comparable to the CER intervention (i.e., 20%). Study participants will see a study dietitian fortnightly for the first 8 weeks and then monthly for the last 16 weeks of the intervention period and will be provided with study foods for 2 days per week. The dietitian will explain the dietary intervention, set goals with participants, discuss strategies to assist with dietary adherence, and monitor progress. At the conclusion of the 24-week intervention, participants will be given practical suggestions and food options for continuing their allocated dietary intervention. Participants will be followed up at 2-, 6- and 12-months’ time during the follow-up period to monitor progress. No food will be supplied to participants during this time.

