### Data sources

3.2.

Key objectives and data sources used to meet the overall aim of this mixed-methods evaluation have been developed in line with similar evaluations (25) and are outlined in Table 1. Qualitative data will be collected and reported in line with the consolidated criteria for reporting qualitative research (COREQ) (26). It is anticipated that data collection will be complete by September 2023. For the purposes of this evaluation, participant “engagement” with the intervention is defined as whether participants: follow the general requirements of the study protocol (e.g., attendance of dietetic consults, self-monitoring); follow the dietary requirements of the intervention; and choose to continue with the intervention (e.g., rates of drop-out).

**Table 1 tab1:** Objectives, data sources and analysis for the evaluation of Shifting Weight using Intermittent Fasting in night shift workers (SWIFt) study.

Objective	Quantitative data source/analysis	Qualitative data source/analysis
1. To describe participant engagement overall and for each of the SWIFt weight loss interventions		
1.1 Dietary review attendance.	Number of dietetic reviews attended (Yes/No). Also described as percentage of reviews attended overall and by intervention group.	
1.2 Dietary goals.	Number of reviews where participant is following dietary goals as assessed by dietitian (Yes/No). Also described as percentage of reviews where goals are met overall and by intervention group.	
1.3 Dietary energy restriction.	Pre- and post-intervention energy restriction: 7-day food diary (baseline compared to 24-weeks and 18-months). Overall and by intervention group.	
1.4 Self-monitoring.	Number of checklists collected. Also described as percentage of food checklists collected overall and by intervention group.	
1.5 Other.	Frequency and percentage of participants who drop-out/time to drop out overall and by intervention group.	
2. Explore factors (intervention features, individual, social, organisational and wider environmental) that influence participant engagement for each of the SWIFt weight loss interventions.		
2.1 Intervention features.	Relationship between intervention group and engagement measures (1.1, 1.2, 1.3, 1.4, 1.5).	Semi-structured interviews. Longitudinal audio diaries (LADs). Features of intervention mapped to the BCT and TDF.

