### Data analysis

3.3.

Quantitative data on participant engagement (see Objective 1 at Table 1) will be analyzed for frequency/count and proportions or as overall daily energy restriction as described above. Regression models will be used to examine associations between engagement measures, participant characteristics (sex, age, ethnicity, occupation, shift schedule, number of night shifts per fortnight, years in night shift), intervention group, and weight change. It is anticipated that general linear regression models will be used for dependent variables that are continuous data and generalized linear regression models will be used for dependent variables that are count data. Differences in drop-out/time to drop out between intervention groups will be examined via survival curve analysis.

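### The energy measure is labelled percent change and energy restriction, but its formula gives percent of baseline, so its descriptive values are wrong as written

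*Protocol article*

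**What the plan says.** Section 3.2.1.3 (Dietary energy restriction) defines the measure. Mean daily intake from the 7-day diary at 24 weeks and at 18 months is to be "divided by the baseline average daily energy intake to provide an estimate of the percent change in energy intake achieved at each time-point". No subtraction of 1 or of 100% follows, and no sign convention is given.

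Two other places name the same quantity differently. Table 1, objective 1.3, lists it as "Pre- and post-intervention energy restriction: 7-day food diary (baseline compared to 24-weeks and 18-months", to be shown overall and by group. Section 3.3 (Data analysis) says engagement data will be summarised as counts and proportions or "as overall daily energy restriction as described above", which sends the analyst back to the formula in 3.2.1.3.

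Section 2 sets a 20% restriction for the continuous arm and a comparable weekly restriction for the two 5:2 arms. Table 1 also places measure 1.3 in the relationships studied under objectives 2.1, 2.2 and 3.1.

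**The concern.** One variable carries three meanings: a ratio (the formula), a percent change (the label in the same sentence) and a restriction (the heading, Table 1 and section 3.3). They take different values for the same participant, and restriction has the opposite direction to the other two.

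This is the only listed engagement measure that quantifies energy intake. Objective 1 is descriptive, so the tabulated value is itself the result. If the formula is followed and the labels are kept, the table shows about 80% *change* or *restriction* in a group that achieved a 20% reduction, and 100% in a group that achieved none. A reader of the association tables who takes the restriction label at face value would also expect a larger value to mean more restriction, when it means less.

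**Working it through.** **Inputs.** From section 3.2.1.3: follow-up mean intake F, baseline mean intake B, stated formula F/B. From section 2: target 20%. The article gives no intake figures, so the kJ values below are assumed for illustration; only the ratio matters. Section 2 does not say what base the 20% is taken from. Here it is taken from baseline intake, because the measure is relative to baseline.

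**Formulas.**
- Stated quantity, as a percentage: 100 × F/B
- Percent change: 100 × (F − B)/B = 100 × (F/B − 1)
- Restriction: 100 × (B − F)/B = 100 × (1 − F/B)

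**Values.**

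| Assumed intake, kJ/day (B to F) | As stated | Percent change | Restriction |
|---|---|---|---|
| 10,000 to 8,000 (20% cut) | 80% | −20% | +20% |
| 10,000 to 10,000 (no change) | 100% | 0% | 0% |
| 10,000 to 11,000 (10% rise) | 110% | +10% | −10% |

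The stated value is always 100 percentage points above percent change. The two rise and fall together. Only restriction runs the other way.

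**Effect on the regressions.** Write R = F/B, C = R − 1 and S = 1 − R. If weight change = a + bR, then it also equals (a + b) + bC, and (a + b) − bS. The slope is b, b and −b; only the intercept moves, and the p-value for the slope is the same. If R is the outcome, replacing it by C lowers the intercept by 1 and leaves every other coefficient alone; replacing it by S reverses their signs.

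An illustrative simulation agrees. Its inputs are all assumed: true baseline 9,000 kJ with SD 1,500, true restriction 20% with SD 10 points, and independent multiplicative diary error of 10%, 20% or 30%. Regressing weight change on the ratio gave slopes of 8.58, 2.98 and 1.30. Percent change gave the same slopes, and restriction gave the same slopes with a minus sign. At 10% error the intercepts were −13.917 (ratio) and −5.337 (change); the difference is 8.58, the slope, as the algebra requires.

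**Baseline diary error.** In the same simulation the correlation with observed baseline intake was 0.27, 0.47 and 0.53 in absolute value, identical for all three forms. Correcting the formula does not remove this link.

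**The case against.** The strongest reply is that this is loose wording. The authors may intend to convert the ratio, and 80% of baseline is one subtraction away from a 20% reduction. The measure is one of several engagement measures in an exploratory evaluation; effectiveness for weight loss belongs to the main trial. No slope or p-value is distorted. All of this is fair and limits the severity. It does not remove the point, because the sentence is written as the definition, section 3.3 refers back to it, and the article states no conversion.

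Several stronger readings are tempting and are not supported:

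- *The direction is wrong.* It is wrong only against restriction. Against percent change, the label in the defining sentence, it is right.
- *The measure runs opposite to every other engagement measure.* Attendance, goals and checklists are scores where higher means more engaged, but drop-out (objective 1.5) also runs the other way, so the plan has no uniform direction to break.
- *Coefficients for objectives 2 and 3 will be read with the wrong sign.* This requires analysts or readers to overlook the stated formula. It is a risk of misreading, not a bias in an estimate.
- *The result cannot be set against the 20% target.* It can, by subtraction from 100%.
- *The ratio understates restriction because diaries are noisy.* With independent lognormal errors, the mean of individual ratios at a true 0.80 is 0.80 × (1 + CV²): 0.808, 0.818, 0.832 and 0.850 at CVs of 10%, 15%, 20% and 25%. The article gives none of these CVs, and positively correlated errors between one person's two diaries would shrink the effect. A correctly defined percent change inherits the same bias (0.832 becomes −16.8%), so it is not a consequence of the mislabelled formula.

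**Conclusion.** The formula in section 3.2.1.3 does not produce the quantity it names. As written, the descriptive values for objective 1.3 are off by exactly 100 percentage points from percent change, and they run opposite to the restriction named in the heading, Table 1 and section 3.3. This follows from arithmetic alone and needs no assumption about the data.

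The consequence is confined to reported values and their interpretation. Linear-model slopes and p-values change at most in sign. Severity is minor to moderate, given the exploratory role of the measure and the ease of recovery from the same data.

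Dependence on baseline diary error is a separate and lesser matter. It affects any measure taken relative to baseline, and its size cannot be computed from the article, which gives no diary error or SD.

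**What to change.** 1. In section 3.2.1.3, replace the definition with one of: percent change = 100 × (follow-up mean intake / baseline mean intake − 1), or restriction = 100 × (1 − follow-up mean intake / baseline mean intake).
2. Use that one name and sign in the section heading, Table 1 and section 3.3, and state which direction means more restriction.
3. Report the achieved value beside the 20% target in section 2.

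Cost: one line of text and consistent labels; no new data.

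As a separate and optional improvement, when energy intake is the outcome, model follow-up intake (preferably on the log scale) with baseline intake (likewise logged) as a covariate, and back-transform to a percentage. Baseline intake is already collected; the cost is one extra model term.

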##### Self-monitoring

3.2.1.4.

Each SWIFt study participant will be provided with food for 2 days of the week totaling approximately 2,100 kJ/day (female) – 2,500 kJ/day (male). For the 5:2 intervention groups, the total energy content of the food to be provided is equivalent to the total energy intake permitted during fasting periods, and is designed to assist with adherence to the intervention. For participants in the CER group, the foods to be provided will be equitable in terms of what will be provided to all participants and, if these foods are consumed, should replace other foods in their diet (i.e., not increase energy intake and form part of their 20% energy restriction for the day). If a participant is unable to attend the clinic facility to collect food (e.g., due to COVID-19 travel restrictions), supermarket vouchers will be provided to allow a participant to buy the food items specified by the study dietitian. For all intervention groups, a food checklist for each week of the 24-week intervention will be provided to participants to note down the food provided, the date/time the food was consumed, the amount consumed (g/ml), and to note down other foods that were also consumed in addition to the study foods on that day. At each study visit, collection of the checklist will be recorded by the study dietitian (yes/no). Each participant will have a score out of 8 (the total number of dietetic reviews over the 24-weeks), representing whether checklists were collected at each visit. See Objective 1.4 in Table 1.

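### Self-monitoring (measure 1.4) is captured as one yes/no at each of 8 unevenly spaced visits, with no threshold for 'yes', and so cannot give the percentage of checklists that Table 1 defines

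*Protocol article*

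**What the plan says.** Three places in the Protocol article bear on this measure.

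- **Section 3.2.1.4 (Self-monitoring), what is issued:** "a food checklist for each week of the 24-week intervention will be provided to participants". That makes 24 lists per participant.
- **Section 3.2.1.4, what is stored:** the dietitian enters yes or no for collection at each study visit, and the entries are summed: "Each participant will have a score out of 8 (the total number of dietetic reviews over the 24-weeks), representing whether checklists were collected". The section then points to objective 1.4 in Table 1.
- **Table 1, objective 1.4, what is reported:** "Number of checklists collected. Also described as percentage of food checklists collected overall and by intervention group".

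Section 2 (Intervention of interest) sets the visits "fortnightly for the first 8 weeks and then monthly for the last 16 weeks of the intervention period".

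Table 1 uses measure 1.4 again as an engagement measure related to intervention group (2.1) and to participant characteristics (2.2), and as a correlate of weight outcome (3.1). Section 3.3 assigns these analyses to regression models.

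**The concern.** One variable has two units. The text counts visits, with 8 as the denominator. The table counts checklists, of which 24 are issued. The table's wording does not look like loose shorthand, because its row for objective 1.2 counts reviews and its row for 1.4 counts checklists.

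A yes/no entry that stands for 2 or 4 weekly lists cannot record partial return, and nothing says whether one, some or all of the lists due make a 'yes'. Different dietitians could apply different rules. Because visits thin out after week 8, an unweighted sum over visits also gives early weeks more influence than late ones.

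Describing and explaining engagement is the purpose of this evaluation. A self-monitoring score that does not correspond to the proportion of lists returned affects the descriptive result by group and every regression in which measure 1.4 is an outcome or a predictor. If only the yes/no is kept, no later analysis can recover the counts from that field.

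**Working it through.** **Inputs.** 24 weekly lists and 8 reviews (section 3.2.1.4). Visits every 2 weeks for 8 weeks, then monthly for 16 weeks (section 2). Monthly is taken as every 4 weeks, which is an assumption.

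**Reproducing the plan's 8.** 8/2 + 16/4 = 4 + 4 = 8 reviews, at weeks 2, 4, 6, 8, 12, 16, 20 and 24. This matches the stated total and supports the 4-week reading. Lists due at each visit are 2, 2, 2, 2, 4, 4, 4, 4, which sum to 24.

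**What a given score can mean.** Table 1 percentage = lists collected / 24.

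| Score | If any list counts as 'yes' | If all lists due are required |
|---|---|---|
| 0/8 | 0% | 0% to 16/24 = 67% |
| 4/8 | 4/24 = 17% to 16/24 = 67% | 8/24 = 33% to 20/24 = 83% |
| 8/8 | 8/24 = 33% to 24/24 = 100% | 24/24 = 100% |

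- The 33% at 8/8 is one list handed in at each of 8 visits.
- The 67% at 0/8 is one list missing at every visit: (4 × 1 + 4 × 3)/24 = 16/24.
- The 83% at 4/8 is all lists at the four monthly visits plus one of two at each fortnightly visit: (16 + 4)/24.

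**Weighting, which does not depend on the threshold.** Each visit is worth 1/8.

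- Weight per week in weeks 1-8: (4/8)/8 = 0.0625.
- Weight per week in weeks 9-24: (4/8)/16 = 0.03125.
- Ratio: 2.
- Full return in weeks 1-8 and none after: score 4/8 = 50%, true 8/24 = 33%.
- None in weeks 1-8 and full return after: score 4/8 = 50%, true 16/24 = 67%.

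**An illustration of practical size.** Suppose the probability of return falls linearly from 95% in week 1 to 35% in week 24. This is assumed; the document gives no return rates. True mean return is (0.95 + 0.35)/2 = 65%. The expected visit score is the average over the 8 visits of P(yes).

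| Rule and dependence within a visit | Expected score |
|---|---|
| Any list counts, weeks independent: P = 1 − Π(1 − p) | 95.9% |
| All lists required, weeks independent: P = Πp | 42.7% |
| All-or-none return within a visit (either rule): P = mean p | 70.2% |

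The last row is the weighting effect alone. Mean return is 85.9% in weeks 1-8 and 54.6% in weeks 9-24, so the score is 0.5 × 85.9% + 0.5 × 54.6% = 70.2%, against 65%.

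**The case against.** The best defence is that section 3.2.1.4 is the operational definition, that it states its denominator, and that Table 1 is a loose label for the same thing. Table 1 never prints the number 24. Scores out of 8 are also used for attendance and dietary goals, which gives a common scale. All arms follow the same visit schedule, so the uneven weighting is the same in each. The evaluation is exploratory, and this is one of five engagement measures.

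Much of this is fair. The 24 is inferred from one list per week, and a visit-level score is a legitimate choice if it is labelled as such. What does not stand is the idea that the two definitions are interchangeable: the table shows that no threshold makes the score out of 8 yield the percentage of lists.

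A reader might go further and infer any of the following, none of which the document supports:

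- **That one-third completion scores 100%.** This needs the rule that any list counts. The text permits that rule but does not state it. Under an all-lists rule the error runs the other way.
- **That the score hides late decline.** This too needs the any-list rule. Under the all-lists rule in the illustration, the expected visit score falls from 0.88 at the first visit to 0.02 at the last, which exaggerates the decline.
- **That the error is 20 to 30 percentage points in practice.** Those gaps rest on independent weeks. Lists handed over together are plausibly correlated, and with all-or-none return the gap is about 5 points.
- **That arms are compared unfairly or the weight association is biased in a known direction.** Nothing in the document establishes either.

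**Conclusion.** The point holds as an internal contradiction with a measurement consequence. Following section 3.2.1.4 as written does not produce the measure that Table 1 objective 1.4 defines, and the threshold for 'yes' is undefined.

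Two results are arithmetic, given the 8 visits, the 24 lists and monthly read as 4-weekly: the ranges of return compatible with one score, and the double weight of each week in weeks 1-8. The practical size is uncertain. For the assumed decline with 65% true return, the score lies between about 43% and 96% according to the threshold and the clustering of returns, and is about 70% when return within a visit is all-or-none.

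The consequence is limited to measure 1.4, its description by group, and the regressions under objectives 2 and 3.1. The randomized comparison of weight is not affected. It should be corrected, because the contradiction is plain and the correction is cheap.

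**What to change.** 1. **Preferred.** At each visit record how many weekly checklists were collected (0-2 at fortnightly visits, 0-4 at monthly visits). Define measure 1.4 as lists collected out of 24, or out of those due before drop-out, and say which. Put the same definition in section 3.2.1.4 and Table 1.
2. **For visits already held.** Count the lists already collected, where they have been retained. Participants write the date of consumption on them, so they can be assigned to weeks, but the article does not say whether they are kept. This step may matter most: section 3.2 expects data collection to finish by September 2023, and the 18-month follow-up comes 12 months after the active phase, so a prospective change may reach few visits.
3. **Where counts cannot be recovered.** State the threshold for 'yes', relabel Table 1 row 1.4 as visits with checklists collected, and weight each visit by the weeks it covers (2 or 4). Weighting removes the double weight of early weeks but not the loss of information on partial return, which should be acknowledged in reporting.

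The cost is a change of one REDCap field from yes/no to a count, and a one-off count of lists on file. No additional burden falls on participants.

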##### Other engagement measures

3.2.1.5.

Participant drop-out will be recorded, including date and reasons for drop-out (if specified). See Objective 1.5 in Table 1.

##### Other SWIFt study quantitative data sources

3.2.1.6.

Other SWIFt study data sources to be used for this evaluation have been described previously as part of the wider SWIFt study protocol (11) and include: weight at baseline, 24-weeks and 18-months; demographics and socioeconomic factors at baseline [age, sex, ethnicity (28), occupation, shift schedule, number of night shifts per fortnight, years in night shift]. See Objectives 2 and 3 in Table 1.

#### Qualitative data sources

3.2.2.

##### Semi-structured interviews

3.2.2.1.

In-depth, semi-structured interviews will be undertaken with participants from each dietary intervention. Three sets of interviews will be undertaken (at baseline, 24-weeks, and 18 months). Each interview is expected to be approximately 30–45 min in duration. An interview guide for each stage of interviews has been informed by existing dietary research in the shift working population (29, 30), the SWIFt pilot study, and the Theoretical Domains Framework (TDF) (see Supplementary material 1). The TDF provides a comprehensive set of determinants of behaviour grouped into constructs that have been derived from a review of relevant behaviour change theories (31). It has been successfully used for designing interview guides for previous evaluations of behaviour change interventions (32) and for analyzing interview data in a shift worker population (29). It is anticipated that interviews will occur either over the phone or via Zoom video-conference (Zoom Video Communications Inc., Version 5.13) at a time convenient to the study participant. The interviews will be recorded and transcribed verbatim (e.g., including ums, ahs, laughter and so on) by the main researcher (CD) or a transcription service. See Objectives 2 and 3 in Table 1.

The purpose of the baseline interview is to explore the motivations of participants for participating in the SWIFt study and perceived enablers or barriers to prior weight management. The interview will also identify what participants are hoping to achieve during the 24-week intervention.

The purpose of the 24-week (post-intervention) interview is to explore the participant’s experience of their allocated dietary intervention. In particular, to explore the perceptions of participants around reasons for engagement/non-engagement to the intervention, study factors thought to have assisted, and contextual factors (e.g., enablers and barriers at the individual, social, organisational, and wider environment) that have thought to influence engagement and weight change outcomes of the study.

The purpose of the 18-month interview is to explore the participant’s experience in following their allocated dietary approach without the support of the study intervention. This will explore the enablers and barriers to following their allocated dietary approach and weight management over this 12-month follow-up period.

